### Trial design

The Operative Vascular Intervention Decision-making Improvement Using Sdm-tools (OVIDIUS) trial design is a 15-center stepped-wedge cluster randomised trial in the Netherlands, as shown in Table 1. Each cluster consists of three participating medical centres. The reasons for choosing this design is in the first place that it allows the evaluation of outcomes before and after introduction of the DSTs in the individual centres and limits the influence of any intercurrent changes in protocols on the clinical outcomes. Second, all participating centres will eventually have implemented at least some of the DSTs and thereby a certain level of SDM.

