### Outcomes

The primary outcome is the level of SDM during the consultation as scored with the 5-item Observing patient involvement (OPTION) instrument [23]. The 5-item OPTION instrument allows researchers to objectively assess the level of patient involvement in the decision-making process as scored from audio-recordings of the consultations [24]. If the vascular surgeon and patient need more than one consultation to reach a treatment decision, all consultations are audio-recorded and scored as one consultation. Afterwards, two researchers independently score the five OPTION-items on a five-point scale. The cumulative OPTION-score is expressed on a 100-point scale.

Baseline characteristics, i.e. age, gender, diagnosis, highest level of education, employment status, social status, and ethnicity, are collected from the patients using a questionnaire before consultation.

Secondary outcomes are patients’ disease specific knowledge, decisional conflict, quality of life, and SDM as perceived by patients, SDM as perceived by vascular surgeons, the treatment decided upon, the implementation of DSTs, and process measures.

The patients’ disease-specific knowledge is scored directly after the consultation. The questions test whether patients correctly understood the information presented in the decision aid or received during the consultation.

Decisional conflict in patients is scored directly after the consultation and is repeated 4 weeks after consultation in which the treatment decision is made [17]. If an endovascular or open surgical treatment takes place within 4 weeks, decisional conflict is scored just before treatment. The decisional conflict in patients is scored using the 16-item Decisional Conflict Scale (DCS) [25].

Quality of life in patients is scored directly after consultation and again 6 weeks after treatment with the Short Form Health Survey (SF12) [26].

SDM as perceived by patients is scored directly after consultation using the SDM-Q-9 questionnaire, the 3-item CollaboRATE questionnaire, and the one-question Control Preference Scale and Control Perception Scale (CPS) [27–29]. The Control Preference Scale documents the desired amount of patient involvement and is scored before the consultation. The Control Perception Scale assesses the actually perceived amount of patient involvement and is scored after the consultation.

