### Sample size

Sample size calculations are based on a clinically relevant difference in the use of SDM during consultation before and after introduction of the DSTs. The systematic review of Couët et al. [31] found a mean increase from 23 (SD 14) to 34 (SD 8) of SDM scored with the 5-item OPTION instrument. An 11 out of 100 points increase of the 5-item OPTION instrument seems a meaningful improvement as it means an increase from a ‘minimal’ to a ‘moderate’ effort to involve patients in the decision-making process [31]. A larger increase would, of course, be even more clinically relevant and would require fewer patients, but this is less likely to reach. With a significance level of 0.05 and a power of 90%, a total sample size of 58 patients is required.

This number needs correction for the stepped-wedge design with cluster randomisation, as opposed to an individual patient randomisation. The total sample size from the power analysis is to be multiplied by the design effect for a stepped wedge trial. The pre-specified number of 5 steps (i.e. 6 time periods) and 5 clusters results in 58/(6*5) = 2 patients, per cluster per time period. Assuming an intermediate-level intra-cluster correlation of 0.01, the stepped wedge design effect is 1.944 [32]. Thus, the total sample size needed in this trial is 58 × 1.944 = 113 patients per disorder. Since four different vascular diseases are studied, there are actually four trials in one trial. Therefore, a multiplication of the total sample size by 4 is necessary, which leads to 452 patients. To adjust for a loss-to-follow-up of 10%, the study aims to include a total of 502 patients.

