### Statistical methods

Baseline characteristics are summarised using descriptive statistics. Unevenly distributed outcome measures are expressed as medians and inter-quartile ranges. A differential effect among the four included vascular diseases is not expected, as the primary outcome is SDM. SDM is equally applicable to each of these diseases since multiple treatment options are available. Nevertheless, the sample size is sufficient to analyse the effect on SDM for each disease separately.

Differences in mean scores of the 5-item OPTION instrument between consultations in which usual care is provided (control group) and the consultations in which DSTs are used (intervention group), are analysed using the Student t-test with Satterthwaite correction for unequal variances. ANCOVA is applied to correct for possible baseline differences in patients before and after the introduction of the DSTs.

Differences in (semi-)continuous variables between the usual care group and the DSTs group (e.g. Likert scales and quality of life scores) are analysed by means of the Student t-test or the non-parametric Mann-Whitney U test, depending on the normality of their distribution. Percentages are compared using a Chi-square test (e.g. for the final treatment choice). In particular, before-after differences in DCS at 4 weeks are analysed after correcting for differences between the groups in baseline DCS. Logistic regression analysis is used to determine the individual effect of the different DSTs on our primary outcome. Statistical analyses will be conducted using IBM SPSS version 24 (IBM, Armonk, NY, USA).

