## Discussion

Vascular surgery is pre-eminently a field in which SDM can enhance quality of care by incorporating patients’ preferences in the decision-making process, since there is commonly a conservative, endovascular or open surgical treatment available for most vascular surgical disorders. Unfortunately, the use of SDM is still limited amongst vascular surgeons. We therefore developed DSTs to assist vascular surgeons and their patients in shared decision-making. The OVIDIUS trial was designed to implement these DSTs into the vascular surgical consultation room and to study their effect on SDM.

Strengths of the OVIDIUS trial are first of all that both the patient advocacy group and the Dutch Society for Vascular Surgery were involved in the development of the DSTs, which is a prerequisite for a nationwide implementation of these DSTs to foster SDM. Second, 15 medical centres throughout the Netherlands participate in this study, including university and general hospitals, thus reducing selection bias by including uncomplicated cases only. Third, the stepped-wedge cluster-randomised study design minimizes the influence of any intercurrent changes in local protocols on the clinical outcomes during the trial period and it ensures that at the end of the study all participating centres have implemented at least some of the DSTs and thereby a certain level of SDM.

Limitations of the OVIDIUS trial are, first a potential inclusion bias of patients. Patients who actively want to be involved in the decision-making process may be more willing to participate, whereas patient who prefer the surgeon to make the decision are less inclined to participate. That is why the preferred decision-making strategy is assessed via the CPS questionnaire prior to consultation. Second, the trial is powered for four different diseases, even though their incidences differ. Hence, the researchers must closely monitor the inclusion rates of these different diseases and take appropriate action when one disease is included much more frequently than another.

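### The primary t-test and patient-level ANCOVA leave out calendar period and centre, so in this stepped-wedge trial any drift in shared decision-making is counted as an effect of the tools

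*Protocol article*

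**What the plan says.** The Trial design section of the protocol article states that the "trial design is a 15-center stepped-wedge cluster randomised trial in the Netherlands", and that "Each cluster consists of three participating medical centres". The Allocations section has the five clusters cross over in random order, one about every 2 months.

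For the primary outcome, the Statistical methods section says that differences in mean OPTION scores between the usual-care and tool consultations "are analysed using the Student t-test with Satterthwaite correction for unequal variances". It then adds: "ANCOVA is applied to correct for possible baseline differences in patients before and after the introduction of the DSTs". The baseline variables, in the Outcomes section, are all patient characteristics: "Baseline characteristics, i.e. age, gender, diagnosis, highest level of education, employment status, social status, and ethnicity". Secondary outcomes get t-tests, Mann-Whitney tests or chi-square tests.

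Clustering enters only in the Sample size section: "This number needs correction for the stepped-wedge design with cluster randomisation, as opposed to an individual patient randomisation". There the protocol takes an intra-cluster correlation (ICC) of 0.01 and a design effect of 1.944. The Discussion counts it as a strength that "the stepped-wedge cluster-randomised study design minimizes the influence of any intercurrent changes in local protocols on the clinical outcomes during the trial period"; the Trial design section gives the same reason for choosing the design.

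**The concern.** A stepped-wedge trial randomises when each cluster switches, so exposure and calendar time are correlated by construction. The design protects against changes over time only if the analysis compares clusters within the same period, that is, if period is in the model. A two-sample t-test pools all control consultations against all intervention consultations, and patient-level ANCOVA cannot restore the within-period comparison. Any general change in how surgeons conduct consultations goes into the estimated effect. The article's own Discussion expects the trial to revive interest in shared decision-making among vascular surgeons.

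The t-test and ANCOVA also treat patients as independent, although they share centres and surgeons, so the reported standard error does not reflect the design. The unadjusted tests for secondary outcomes have both faults. This is not a detail left to an analysis plan: the article names a specific method, and an analysis plan could be right only by contradicting it.

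**Working it through.** **Inputs.** From Sample size: 5 clusters, 6 periods, 2 patients per cluster-period, SDs 14 and 8, ICC 0.01, design effect 1.944, and 113 patients per disorder or 452 over four. Assumptions of this review: the standard layout (cluster *i* has *i* control periods, then 6 − *i* intervention periods), because Table 1 is not shown; equal cell sizes; two-sided 5% tests; and a common variance of (14² + 8²)/2 = 130.

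**1. What the sample size paid for.** With ICC ρ, *k* = 5 steps, one baseline period, one measurement per step and *n* = 2, the standard stepped-wedge design effect is

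[1 + ρ(kn + n − 1)]/[1 + ρ(kn/2 + n − 1)] × 3(1 − ρ)/[2(k − 1/k)] × 6
= (1.11/1.06) × (2.97/9.6) × 6 = 1.944.

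This reproduces the protocol's figure, and 58 × 1.944 = 113, × 4 = 452, /0.9 = 502. The same 1.944 is obtained as the variance of the effect estimate in a model with fixed period effects and a random cluster effect, divided by the t-test variance.

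Most of it is the price of period adjustment. At ρ = 0 the formula gives 3/(2 × 4.8) × 6 = 1.875. Directly: the share of clusters exposed in the six periods is 0, 0.2, 0.4, 0.6, 0.8 and 1, so the mean within-period exposure variance is (0 + 0.16 + 0.24 + 0.24 + 0.16 + 0)/6 = 0.1333, against 0.25 overall, and 0.25/0.1333 = 1.875.

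**2. Bias from calendar time.**
- Mean period, control: (5·1 + 4·2 + 3·3 + 2·4 + 1·5)/15 = 35/15 = 2.33.
- Mean period, intervention: (1·2 + 2·3 + 3·4 + 4·5 + 5·6)/15 = 70/15 = 4.67.
- The gap is 2.33 of the 5 steps from first to last period, so a linear drift of D points biases the t-test by (7/15)·D = 0.47·D.

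**3. False positives with no true effect.** The t-test variance is 4 × 130/N, so the SE is 1.07 at N = 452 and 2.15 at N = 113. The drift sizes are assumptions; the protocol gives none. Ranges run over independence and ICC 0.01 at cluster or centre level.

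| Drift over the trial | Bias | N = 452 | N = 113 |
|---|---|---|---|
| 2 points | 0.93 | 14–16% | 7–8% |
| 5 points | 2.33 | about 58% | 19–20% |

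**4. Clustering alone, no drift.** In the raw difference of means, cluster *i* has net weight (6 − 2*i*)/15. The sum of squares is (16 + 4 + 0 + 4 + 16)/225 = 0.1778. The true variance is therefore (1 − ρ)·520/N + ρ·130·0.1778, with the last term divided by 3 if the correlation sits in 15 independent centres. At N = 452 and ρ = 0.01:
- 5 clusters: 1.139 + 0.231 = 1.370, SE 1.17.
- 15 centres: 1.139 + 0.077 = 1.216, SE 1.10.

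| ICC | Type I error, 5 clusters | Type I error, 15 centres |
|---|---|---|
| 0.01 (protocol) | 7.2% | 5.7% |
| 0.05 (assumed) | 16% | 8.4% |
| 0.10 (assumed) | 25% | 12% |

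**5. With period and cluster or centre terms.** In simulation (3000 runs, 450 patients, trends of 0, 1 and 2 points per period, ICC 0.01 and 0.05) the estimate was unbiased and type I error was 4.5–5.8%. The theoretical SE at N = 452 and ICC 0.01 is 1.63 (5 clusters) or 1.54 (15 centres).

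**The case against.** Several limits on the size of the problem are fair.

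- At the protocol's own ICC the standard-error fault is small. Centres were drawn into clusters by lot, so the milder 15-centre figures are the more natural ones, and the larger rates need ICCs that the article does not give. This stands: calendar time is the main problem.
- The 58% depends on an assumed 5-point drift and on the pooled 452 patients. For one disorder, the level at which the sample size was set, the rate is about 20%. This also stands.
- Linear drift would have to reach 10/0.467 = 21 to 11/0.467 = 24 points to produce the whole planned 10- to 11-point effect. So modest drift could not explain a large observed effect in full; it would still distort its size, and a small significant effect would remain ambiguous.
- The expected renewed interest comes with no size or timing, and it need not raise scores in centres still under usual care. Correct, but the analysis has no means of showing whether it does.
- Table 1 is not shown and steps may slip by 2 months, so the factor 0.47 is an assumption. Another layout would change the factor, but control would still precede intervention in every centre.
- The source of the design effect is not available here. Its exact reproduction from the period- and cluster-adjusted variance answers this.

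None of these points supplies a period or centre term.

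**Conclusion.** The concern holds and must be fixed before analysis. The stated primary analysis does not use the feature of the design that the article offers as its protection against changes over time, and it does not match the analysis for which the sample was inflated. The confounding is structural, with a bias of 0.47 times any linear drift under equal cells. What that means in false positives depends on a drift the protocol does not quantify: 14–16% at 2 points and about 58% at 5 points with 452 patients, less for a single disorder. The understated standard error is a secondary fault at ICC 0.01 and grows if the true ICC is higher.

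**What to change.** Replace the t-test and ANCOVA for the primary outcome with one pre-specified linear mixed model for the OPTION score, with:
- condition as allocated (before or after the cluster's crossover);
- fixed effects for calendar period;
- disease as a fixed effect;
- a random intercept for centre;
- Satterthwaite or Kenward-Roger degrees of freedom.

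Period and centre are essential. A surgeon random intercept and a residual variance that differs by condition (the plan assumes SDs of 14 and 8) are useful refinements if the data support them. Use the same structure, with a logistic or ordinal link where needed, for secondary outcomes. Keep the t-test as a descriptive summary only.

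The cost is a rewritten paragraph and modest analysis work; centre and consultation date are known for every patient. The standard error at N = 452 and ICC 0.01 rises from 1.07 to 1.54–1.63 (not computed with a surgeon term). No extra patients are needed on the protocol's inputs: power stays above 99% at N = 452. For one disorder (N = 113, SE 3.04 with 5 clusters) it is about 91% for 10 points, since 10/3.04 − 1.96 = 1.33, and about 95% for 11 points.

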SDM as perceived by vascular surgeons is scored after the consultation using the SDM-Q-DOC questionnaire and the Control Perception Scale [29, 30].

The treatment decided upon is derived from the audio recording of the consultation. The actually received treatment is obtained from the participating vascular surgeon or centre.

The extent in which DSTs are implemented is determined by scoring the number of times a specific tool is used as recorded by the audio recording (consultation card and decision cards). Successful use of the decision aid is defined as completion of the decision aid by the patient. Completion and time to complete is recorded automatically when patients access the decision aid via the provided link.

Process measures studied are the number and duration of consultations necessary to decide upon a treatment, as obtained from the audio recording(s) or from the participating vascular surgeon or centre.

All outcomes mentioned above are evaluated at the individual participant level.

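### Treatment choice is compared between conditions by a Chi-square test with no term for diagnosis, although the mix of the four diseases may differ between the control and DST data

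*Protocol article*

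**What the plan says.** The Outcomes section lists treatment decided upon among the secondary outcomes: "SDM as perceived by vascular surgeons, the treatment decided upon, the implementation of DSTs, and process measures". It also gives the source: "The treatment decided upon is derived from the audio recording of the consultation". Statistical methods then fixes the test: "Percentages are compared using a Chi-square test (e.g. for the final treatment choice". The paragraph in which this stands frames its comparisons as "between the usual care group and the DSTs group" and does not mention diagnosis.

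The same section speaks of disease in two places, both about shared decision-making (SDM). One is "A differential effect among the four included vascular diseases is not expected, as the primary outcome is SDM". The other is that "the sample size is sufficient to analyse the effect on SDM for each disease separately". Baseline adjustment appears once, directly after the t-test on the OPTION score: "ANCOVA is applied to correct for possible baseline differences in patients before and after the introduction of the DSTs". A logistic regression is also named, but for the effect of the individual tools on the primary outcome.

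Three other statements bear on disease mix:

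- Trial setting admits centres that care for as few as one of the four diseases.
- The Discussion acknowledges that incidences differ and says that the researchers must monitor inclusion by disease and "take appropriate action when one disease is included much more frequently than another". The form of that action is not given.
- Outcomes lists diagnosis among the baseline characteristics collected.

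**The concern.** The argument that the effect should be the same in all four diseases is made for SDM, which can be scored alike in any consultation. It does not carry over to the treatment chosen. A patient with claudication and a patient with a large aneurysm face different options, and there is no reason to expect the same proportion to choose an invasive one. A percentage taken over all four diseases therefore depends on which diseases make it up.

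That would be harmless if each condition held the same mix. A stepped wedge does not secure this, because condition is linked to calendar time and to centre. If the mix changes over time, or differs between clusters that cross over early and late, the overall percentage can move with no change inside any disease. It can equally stay still while a real change takes place. The Background cites fewer invasive choices as a known effect of SDM, so readers are likely to look at this outcome.

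**Working it through.** **Inputs from the protocol.** Five clusters, six periods, significance level 0.05 (taken as two-sided), and 452 patients before the allowance for loss. That figure reproduces: 58 × 1.944 = 112.8, rounded to 113 per disease; 113 × 4 = 452; 452 / 0.9 = 502.2, against the stated 502. Half of 452 is 226 per condition. No figure is given for treatment choice itself.

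**Inputs assumed.** Disease mix, invasive rates, equal cluster-period sizes, independent patients, and no DST effect within any disease.

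**Step 1: how condition is tied to time.** In periods 1 to 6 the number of clusters under control is 5, 4, 3, 2, 1, 0, and under DSTs 0, 1, 2, 3, 4, 5; each sums to 15. Periods 4 to 6 hold (2+1+0)/15 = 20% of control and (3+4+5)/15 = 80% of DST observations. A step change in mix at period 4 thus appears between conditions at 0.8 − 0.2 = 0.6 of its calendar size.

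**Step 2: how condition is tied to centre.** The first cluster to cross over supplies 1/15 of control and 5/15 of DST data; the last supplies the reverse. If the first cluster's share of one disease exceeds that of the other clusters by d points, the conditions differ by (5/15 − 1/15) × d = 0.27d. The order is randomised, so this is chance imbalance without a preferred direction, but with five clusters it need not be small.

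**Step 3: what a shift does to the Chi-square test.** Assume an early mix of aneurysm/carotid/claudication/varicose veins of 15/10/50/25%, one invasive rate for claudication and a common higher rate for the other three. Then

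spurious difference = (rate in others − rate in claudication) × (claudication share under control − claudication share under DSTs).

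Example: claudication is cut to 20% from period 4 (later mix 30/30/20/20). Control share = 0.8 × 0.50 + 0.2 × 0.20 = 0.44; DST share = 0.2 × 0.50 + 0.8 × 0.20 = 0.26. With rates of 80% and 30%, the difference is 0.50 × 0.18 = 9.0 points (58.0% against 67.0%). With 226 per group, the standard error is √(2 × 0.625 × 0.375/226) = 0.0455 under equality and √((0.58 × 0.42 + 0.67 × 0.33)/226) = 0.0453 otherwise. Rejection probability = Φ((0.090 − 1.96 × 0.0455)/0.0453) ≈ 0.51.

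Spurious difference in points and false-positive rate (20,000 simulations for each case with a shift, in agreement with the formula):

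| Recruitment | Claudication share, control / DST | Rates 80% vs 30% | 70% vs 40% | 60% vs 50% |
|---|---|---|---|---|
| No shift | 50% / 50% | 0; 5% | 0; 5% | 0; 5% |
| Gradual move to equal mix | 43% / 32% | +5.8; 24% | +3.5; 12% | +1.2; 6% |
| Claudication 20% from period 4 | 44% / 26% | +9.0; 51% | +5.4; 21% | +1.8; 7% |
| No claudication from period 4 | 40% / 10% | +15.0; 93% | +9.0; 50% | +3.0; 10% |

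With equal rates in all diseases the test stays at 5% in every row. A Cochran-Mantel-Haenszel test stratified by disease stays between 4.7% and 5.2% throughout.

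**Step 4: a shift that cancels.** Take varicose veins/claudication/aneurysm/carotid at 40/30/15/15%, with invasive rates of 90/30/75/75%. The overall share is 0.360 + 0.090 + 0.1125 + 0.1125 = 0.675. At 25% each it is 0.225 + 0.075 + 0.1875 + 0.1875 = 0.675. The mix is fully rebalanced and the overall percentage does not move.

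**The case against.** A journal article condenses the full protocol, and strata for a secondary outcome are a detail that the analysis plan may settle. It also never says in words that the four diseases are combined, and the Sample size section calls the study four trials in one. This limits the point but does not remove it. The article does not leave the method open: it names the test and gives treatment choice as the example, and an ordinary Chi-square test has no place for diagnosis. The remark about four trials concerns the sample size for the OPTION score. ANCOVA is attached to that score and does not apply to a comparison of percentages.

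A reader might infer that the protocol's own rule makes the disease mix shift. The text does not support that. The sentence in the Discussion is conditional and names no action; extra effort on rarer diseases, or action before the first crossover, would fit it as well as slowing a common one, and Recruitment has consecutive patients screened. A reader might also infer that rebalancing must bias the result, or must do so in one direction. Step 4 shows that it need not. Nor is it a fair illustration to move 20 points from varicose veins to claudication in the Step 4 mix. That gives a fall of 0.20 × (90 − 30) = 12 points and about 75% false positives, but it ends at 20/50/15/15, further from balance than it began.

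Two further objections stand. The outcome is secondary, with no power or direction stated for it. And diagnosis alone is not the whole remedy, since the Chi-square test also ignores centre and calendar period.

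**Conclusion.** The point holds in conditional form. The stated test for treatment choice has no term for diagnosis, the by-disease analysis and ANCOVA in the same section cover only SDM and the OPTION score, and condition is tied to calendar time and centre by design. Disease mix may therefore differ between conditions and be read as a difference in treatment choice, or mask one.

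Size and direction cannot be derived from the documents. Under assumed mixes and rates, with 226 independent patients per condition and no DST effect, the false-positive rate is 5% when the mix does not shift, the rates are equal or the shifts cancel. It is about 6% to 24% for a gradual move to an equal mix, and reaches 51% to 93% only for large shifts with very different rates. The primary outcome is not affected by this point. It is worth correcting because it concerns a stated method and the remedy is nearly free.

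**What to change.** In Statistical methods, replace the Chi-square test for treatment choice with a comparison stratified by or adjusted for diagnosis. A logistic model with study condition and diagnosis would do, ideally also with calendar period and centre; a Cochran-Mantel-Haenszel test stratified by diagnosis is the minimum. The minimum deals with disease mix only, which is why the fuller model is preferable in a stepped wedge.

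Report the treatment categories by condition within each of the four diseases, keeping conservative, endovascular and open treatment apart where they apply, so that a shift between the last two is not lost in a two-way split. Show the number of patients by diagnosis, condition and period alongside, so that readers can see whether the mix moved.

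The cost is a sentence or two of analysis text, one model and one table, all from data already collected. No patients or procedures are added.

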### Interventions

The intervention comprises a set of DSTs, developed to help both vascular surgeons and patients to improve SDM. Use of the DSTs is compared to standard care at the level of individual participants. Standard care may include informative leaflets or websites that participating medical centres already provide to their patients.

The DSTs studied here are decision aids, consultation cards, decision cards and a practical training. The patient advocacy society (Heart and Vascular Group) and the Dutch professional society (Dutch Society for Vascular Surgery) provided intellectual support for the development of the DSTs. The Netherlands Organisation for Health Research and Development provided financial support (ZonMw, grant 516,022,506). The participating centres may decide which combination of DST they prefer to use.

*Decision aids* are validated web-based applications that provide patients with information about their disease and treatment options. In addition, it has an interactive section in which the patient is encouraged to consider what he or she believes is important when deciding on a treatment strategy [9, 17]. Patients receive the decision aid prior to the decision-making consultation via a personalised web link. The researchers automatically receive the answers given by patients in the decision aid regarding their disease-specific knowledge and treatment preferences. The following link provides access to the English version of the Dutch decision aid used in this study for patients with an AAA: https://sdmstaging.medify.eu/surgery1/index_da-aortic-aneurysm_en.html

More information about other available decision aids is provided at the website of the Ottawa Hospital Research Institute [18].

*Consultation cards* are validated tools, also known as Option Grids™ [19]. These are A4-sized paper sheets showing questions -with their answers- that patients most frequently ask about the treatment options, presented in a table format. Vascular surgeon and patient discuss the consultation cards during the consultation. The order in which the patient wants to discuss the questions provides insight into the aspects patients find relevant to them personally when deciding on a treatment strategy [11]. Table 3 shows the consultation card used in this study by vascular surgeons for patients with symptoms of intermittent claudication. More information about other available decision aids is provided at the website of the Dartmouth Institute [20].

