**Fig. 1 Fig1:**
[figure not shown]
Carotid artery disease decision cards

*The practical training* is offered to all vascular surgeons, physician assistants and nurse practitioners in the participating centres. The training allows participants to practice the three important steps of SDM, which are the ‘team talk’, ‘option talk’ and ‘decision talk’ [22]. The participants practice these steps with a patient actor under the guidance of a medical psychologist [12, 22]. The practical training takes place just before the vascular surgeons start using the DSTs in their centre.

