### Participants’ timeline

Figure 2 provides an overview of the participants’ timeline. Patients in the intervention group receive the decision aid prior to the appointment at the outpatient clinic. Patient follow-up is finalised after the patient has completed the final questionnaire. Patients receive the final questionnaire 6 weeks after the treatment or, in case of conservative treatment, 6 weeks after the decision-making consultation.

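### The 4-week decisional conflict comparison is corrected for a baseline DCS that is scored after the decision support tools have been delivered, so it does not estimate their total effect at 4 weeks

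*Protocol article*

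**What the plan says.** The analysis rule is in Statistical methods: "before-after differences in DCS at 4 weeks are analysed after correcting for differences between the groups in baseline DCS".

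The measurement schedule is in Outcomes: "Decisional conflict in patients is scored directly after the consultation and is repeated 4 weeks after consultation in which the treatment decision is made". One exception moves the second score earlier: "If an endovascular or open surgical treatment takes place within 4 weeks, decisional conflict is scored just before treatment". The text describes no other DCS measurement. The items that Outcomes places ahead of the consultation are age, gender, diagnosis, education, employment, social status, ethnicity and the Control Preference Scale. DCS is not among them.

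The timing of the tools is given under Interventions and Participants' timeline:

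- Decision aid: "Patients receive the decision aid prior to the decision-making consultation via a personalised web link".
- Consultation cards: "Vascular surgeon and patient discuss the consultation cards during the consultation". Decision cards are described as serving the same purpose.
- Training: "The practical training takes place just before the vascular surgeons start using the DSTs in their centre".

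Centres may choose which combination of these they use.

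**The concern.** A baseline covariate is useful because treatment cannot have changed it. A group difference in it is then imbalance, and correcting for it removes noise or confounding. The first DCS does not have that property. By the time it is scored, an intervention patient has been sent the decision aid, has had the consultation with any cards the centre uses, and has seen a clinician who was offered the training. A lower score in the DST group at that point is what the tools are meant to produce.

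Correcting the 4-week comparison for that score holds part of the intervention's effect constant. The result answers a narrower question: how the groups differ at 4 weeks among patients with the same conflict just after the consultation. If it is reported as the DST effect on decisional conflict, a lasting benefit will look smaller than it is.

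**Working it through.** **Step 1: order of events.** From the sections cited above, for an intervention patient: training of clinicians → decision aid sent → consultation, with cards if used → first DCS → second DCS at 4 weeks or just before earlier invasive treatment. Every tool precedes the first DCS, whichever combination the centre chose. As the text gives no earlier DCS, the baseline DCS in the analysis rule can only be the post-consultation score.

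**Step 2: what the adjusted comparison estimates.** The protocol gives no DCS effect, standard deviation, correlation or power, so there is no stated figure to reproduce. Let

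- d_post = reduction in post-consultation DCS caused by the DSTs,
- d_4wk = total reduction at 4 weeks,
- b = within-group slope of the 4-week DCS on the post-consultation DCS (equal to the correlation when the two SDs are equal).

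Then

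adjusted effect = d_4wk − b·d_post

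share of d_4wk retained = 1 − b·(d_post/d_4wk)

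**Step 3: range.** b and the ratio d_post/d_4wk are assumptions. Share retained:

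| b | ratio 0.5 | ratio 1 | ratio 1.5 |
|---|---|---|---|
| 0.2 | 0.90 | 0.80 | 0.70 |
| 0.3 | 0.85 | 0.70 | 0.55 |
| 0.5 | 0.75 | 0.50 | 0.25 |
| 0.7 | 0.65 | 0.30 | −0.05 |
| 0.8 | 0.60 | 0.20 | −0.20 |

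For equal effects at both times (ratio 1) the share removed is simply b, so 20% to 80%. Over the whole grid it runs from 10% (b = 0.2, ratio 0.5) to 120% (b = 0.8, ratio 1.5). A negative entry means the sign has reversed, which requires d_4wk < b·d_post.

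**Step 4: simulation check.** With 400,000 simulated patients, unit SDs and a true effect of −0.40 SD at both times, least squares with the post-consultation score as covariate gave −0.28, −0.20 and −0.12 at correlations 0.3, 0.5 and 0.7. The formula gives −0.40 × 0.7 = −0.28, −0.40 × 0.5 = −0.20 and −0.40 × 0.3 = −0.12. Using the change score as the response with the same covariate gave identical group coefficients.

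**Step 5: precision against bias.** Adjustment does shrink the residual SD, by the factor √(1 − b²) when SDs are equal. For an equal effect at both times, the ratio of effect to standard error is multiplied by (1 − b)/√(1 − b²) = √((1 − b)/(1 + b)): 0.73 at b = 0.3, 0.58 at 0.5 and 0.42 at 0.7. The loss of effect outweighs the gain in precision. As an illustration, assume an effect of 0.3 SD and 226 patients per group (half of the 452 in Sample size), with clustering ignored. Power is 89% without the covariate, and 65%, 45% and 27% with it at those three slopes.

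**The case against.** Several points can be made for the plan, and some limit the conclusion.

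- **The early effect is not lost.** Statistical methods has a general rule for comparing (semi-)continuous variables between groups, and the post-consultation DCS falls under it. This stands: only the 4-week effect is misestimated.
- **The before-after wording is ambiguous.** It may mean change within a patient, or before and after DST introduction, which is how the article uses the phrase elsewhere. This does not rescue the rule. The covariate is the same under both readings, and with covariate adjustment so is the group coefficient.
- **Change after the consultation may be the question of interest.** That is legitimate, but it is not the effect of the DSTs on decisional conflict, and the article does not present it as a separate question.
- **Fig. 2 may show an earlier DCS.** The figure is not visible in the text reviewed. An earlier DCS there would contradict the Outcomes section, and the two would need to be reconciled.

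A reader might also infer more than the document supports:

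- **That most of the effect is removed.** Most would need b·(d_post/d_4wk) above 0.5. No DCS figures are given to establish that, and with equal effects and b up to 0.5 it is not met.
- **That all of a sustained effect is removed.** That holds for an unadjusted change score, d_4wk − d_post. The plan specifies a correction for the first score, not a plain change score.
- **That any drift back towards usual care would look like harm.** It would not. At b = 0.5, more than half of the early effect must have disappeared by 4 weeks before the sign turns.
- **That this is the trial's leading patient-reported result.** Outcomes lists DCS among several secondary outcomes and ranks none of them.
- **That the SF-12 has the same fault.** Its first score is also post-consultation, but no correction for it is stated.

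**Conclusion.** The concern holds, within limits. On the article's own schedule, the covariate it calls baseline DCS is a post-intervention outcome. Correcting for it removes the part of the 4-week effect already present after the consultation. This is a stated rule that is wrong as written, so it is not detail left to a statistical analysis plan.

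The direction is clear: whenever the DSTs lower the first score and the two scores are positively related within groups, the estimated 4-week benefit is too small. The amount is not known. The 20% to 80% range rests on assumed slopes of 0.2 to 0.8 and an equal effect at both times; unequal effects widen it. The consequence is confined to one secondary outcome. The primary OPTION comparison does not use this covariate.

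**What to change.** In Statistical methods, delete the correction for baseline DCS. Compare the DST and usual-care groups on the post-consultation DCS and on the 4-week DCS as two separate outcomes. Adjust only for variables collected before the consultation, such as age, gender, diagnosis and education. If change after the consultation is also of interest, report it as a separate analysis, labelled as such, and not as the DST effect on decisional conflict.

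The change is one of wording and needs no new data. Its cost is some precision in the 4-week comparison: with equal SDs the standard error no longer shrinks by √(1 − b²), which is 0.87 at b = 0.5. No change is needed to the SF-12 analysis, and none to the primary analysis on this account.
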